| **2.1**  **Research question/objective(s) of the study** | The aim is to assess the association between antibiotic use and risk of subsequent urinary tract infections in adults.  ***Background***  Urinary tract infections (UTIs) encompass a spectrum of infectious syndromes that affect the urinary tract anywhere from the urethra to the kidneys and are one of the most common infections, particularly in primary care (Al Hawati, Blair & Larnard). In 2023, the UTI incidence in primary care was 20 cases per 1.000 registered men and 117 cases per 1.000 registered women (Nivel, 2024). Not only is the UTI incidence higher in women than men, it also increases with age (Ahmet et al., 2018).  Women are particularly susceptible due to the close proximity of the rectum to the urethra as well as a relatively short urethral length (Li & Leslie, 2023). It is reported that 50-60% of women have at least one UTI in their lifetime (Al Hawati, Blair & Larnard, 2023). Most UTI are caused by bacteria from the gut  (Worby et al. 2022).  Most patients with UTIs can be treated relatively simple with oral antibiotics, although treatment failure occurs. Around 20-30% of women with an initial UTI will experience a recurrent UTI within 3-4 months of initial infection (Foxman, 2003). Furthermore, some UTIs can become complicated through a pyelonephritis, prostatitis, and urosepsis, which are associated with morbidity and mortality (Sabih & Leslie, 2023).  A healthy vaginal microbiota is low-diverse and dominated by *Lactobacillus crispatus*.  Vaginal lactobacilli have been touted to prevent invasion of uropathogens, for instance by creating an acidic environment. Disruption of the vaginal ecosystem, causing an overgrowth of anaerobic bacteria or yeasts, increases the risk of vaginal infections such as sexually transmitted infections (Stapleton, 2016, Herthelius 1988). Conversely, treatment that restores a Lactobacillus-dominated microbiota is associated with lower risk of recurrent UTIs. Usage of antibiotics can alter the microbial community (Chee, Chew & Than, 2020).  In pre-menopausal women, factors related to sexual behaviour are major risk factors for UTIs. These include: having a new sexual partner, increased frequency of sexual intercourse as well as the use of spermicide-containing contraceptives (Hooton, 2001). Sexual behaviour is less firmly associated with UTIs in post-menopausal women, where age-, hormonal- and disease-related urogynaecology and immune factors play a more prominent role. An increased postvoid residual urine volume, the presence of bladder prolapse and urinary incontinence have been associated with UTIs (Athanasiou et al., 2010). Antibiotic use or treatment of asymptomatic bacteriuria has also been associated with the development of UTIs (Cai et al., 2014, Smith et al. 1997).  To date, only one small-scale study has been conducted on this subject, which indicated a potential correlation between antibiotic use and an elevated risk of urinary tract infections in pre-menopausal women (Smith et al. 1997). To our knowledge, there are no studies whether this also holds for postmenopausal women and men.  In this study, we would like to evaluate whether different antibiotics (either to treat UTI or other infections) are associated with increased risk of UTI in premenopausal women, postmenopausal women and men. If this association can be confirmed, the next would be to study effective preventive measure for an UTI. This would be highly beneficial, as urinary tract infections represent a significant burden for patients, while antibiotic use is also the major contributing factor to the development of antibiotic resistance. |
| --- | --- |

1. **Study design**

| **3.1**  **a. General description of the study design** | This research project will use the data infrastructure Extramural Leiden Academic Network (ELAN).  ELAN provides access to and the use of pseudonymized healthcare data from various cooperating partners such as healthcare data of general practitioners. The study period concedes 2014-2024.  ***Question***  Is antibiotic use associated with increased risk for urinary tract infection in adults?  Further explorations will be done to what extent the increased UTI risk of antibiotic use holds for:   - Different antibiotics or antibiotic classes - Men versus women - Post- versus Premenopausal women - Indication for antibiotic treatment (excluding UTI’s)   A self-controlled cases series (SCCS) design will be employed to establish the risk for developing an UTI within 3 months after antibiotic treatment compared to patients with an UTI who did not receive an antibiotic treatment. With the SCCS design, patients will be their own control.  The primary endpoint is risk of a UTI within 3 months after initiation of antibiotic treatment computed as an odds ratio.  An antibiotic treatment is defined as the exposure. An UTI between 2 weeks and 3 months after antibiotic treatment is defined as an event. The first 2 weeks after start of the treatment, patients are still somewhat protected by the antibiotic use against a new infection. And if a new antibiotic treatment is needed within 2 weeks after start of treatment, this is considered as treatment failure of the initial treatment.  Descriptive analysis will be performed for exposures, outcomes and covariables for the whole population of analysis and stratified by antibiotic use or not.  Multivariable logistic regression analysis will be performed to assess whether there is an association of antibiotic use with developing a UTI within 3 months after initiation of treatment. First a crude model will be used followed by confounder adjusted models. Confounders are season variability (Winter, spring, summer and autumn) and risk factors for UTI and selected based on theory or literature (Tj VanderWeele 2019). Risk factors are a history of an UTI, urine incontinence, urolithiasis, pregnancy, urine catheter, anatomical / functional abnormality urinary tract, immunocompromising comorbidities such as HIV/AIDS ,Type 2 Diabetes Mellitus.  **Subgroup analysis**  Subsequently, subgroup analysis will be performed to examine whether the association differs upon specific type of antibiotic treatment. For each subgroup, we will calculate an odds ratio for an UTI after antibiotic treatment. Subgroups are antibiotic(group)s, gender and age, type of infection and social determinants .  *Most used antibiotic(group)s in primary care*:   - Amoxicillin - Amoxicillin/clavulanic acid - Flucloxacillin - Tetracyclines - Macrolides - Fluoroquinolones - Trimethoprim - Co-trimoxazole - Fosfomycin - Nitrofurantoin   *Type of infection*   - All infections - UTI - non-UTI (all other infections)   *Gender and age*   - Men - Premenopausal women, defined as < 50 years of age - Postmenopausal women, defined as ≥ 50 years of age   *Social determinants*   - Socio-economic status (SES) - Migrant background |
| --- | --- |
| **3.2**  **a. When will the study be conducted?**  **b. What is the intended end date of the study?** | The research will be performed as part of a MSc. Internship ([name]) in the period between February 2025 and June 2025.  Month 1 – Literature research, writing the introduction, first part of data preparation.  Month 2 – Writing the introduction and methodology, second part of data preparation.  Month 3 – Completing the introduction, methodology and data preparation, start of data analysis.  Month 4 – Completing the data analysis and writing the results.  Month 5 – Writing the report, focusing on the discussion.  The end date is July 2025. |
| **3.3**  **Does the study involve exclusively existing (patient) data (retrospective) and not data yet to be generated (prospective)?** | This study includes already existing data only, and is thus retrospective (see also 3.1). |
| **3.4**  **What type of data will be used for the research?** | Pseudonymized routine care patient data from GP practices participating in ELAN. |
| **3.5**  **If information from patient records is used: describe what type of information is involved.** | The dataset from ELAN contains data over a period of 10 years and includes:   - Number of all included patients in ELAN per year - All patients with an UTI   - ICPC code U70, U71, including subcodes   - Date of registration with GP office - Antibiotic prescriptions ATC J01 for all patients with an UTI   - Corresponding medical diagnosis with the antibiotic prescription by ICPC code   - Details on the antibiotic prescription (name of antibiotic, dose and duration) - Characteristics of included patients   - Year of birth   - Year of death   - Sex   - Referral to urologist for recurrent UTIs   - Risk factors for an UTI     - History of UTI ICPC code U70, U71     - Urine incontinence ICPC code U04     - Urolithiasis ICPC code U95     - Urine catheter ICPC code U28     - Anatomical / functional abnormality urinary tract ICPC code U85     - Type 2 Diabetes Mellitus ICPC code T90.02     - Prostate hypertrophy ICPC codes Y06, Y85     - Medication use for miction problems with ATC codes     - G04BD     - G04C     - Social economic status     - Migrant background |
| **3.6**  **To which time period do the data relate?** | The period between 2014 and 2024 |

1. **Data storage and privacy**

| **4.1**  **a. In the context of this study, will patients/participants be asked for consent to use their (medical) data?**  **b. If no consent is requested: please explain why consent will not be sought.** | In general, it can be stated for the ELAN data warehouse that, in accordance with current guidelines, patients are given the opportunity, through an informed opt-out procedure, to NOT make their pseudonymized and coded data available for scientific research. To inform patients, (digital) posters are hung in the waiting rooms. There are also leaflets available that patients can take with them. The information also appears on the websites of the practices (see supplement A).  Not applicable |
| --- | --- |
| **4.2**  **Have patients/participants previously been asked for consent to use their (medical) data for scientific research?** | See 4.1 |
| **4.3**  **a. Is there (or has there been) a treatment relationship between the researcher(s), or the researcher(s)’ department, and the patients whose records are being reviewed? (see also section 4.8 below)**  **b. Is the treatment relationship still ongoing, or has it since been terminated?** | Yes, two of the researchers ([name], [name]) worked as a general practitioner in the region where the research is done. Next to pseudonymization of patients, details on GP and GP practice is pseudonymized as well.  The principle investigator of this project has stopped working in one of the ELAN data warehouse practices and there is no longer a treatment relation. |
| **4.4**  **Is it likely that patients from the study population have since passed away?** | Yes, this is a possibility. |
| **4.5**  **For how many patients will data be used?** | The study will use data of all patients of 18 year and older in the ELAN data warehouse. |
| **4.6**  **Have patients had the (general) opportunity to object to the (coded/anonymized) use of their (medical) data?** | Yes, within the framework of the ELAN data warehouse, registered patients are informed by participating GPs about the reuse of their medical data for scientific research, with leaflets and posters. Hereby they are offered the opportunity to lodge an objection (informed opt-out procedure). |
| **4.7**  **Is the use of (medical) data for scientific purposes recorded in the medical record of the relevant patient(s)?** | No explicit note is made per patient in the EPD of the general practitioner, because most general practitioner systems are not (yet) designed for this. It is, however, recorded which patients object to reuse their data for research and it is not used for research. |
| **4.8**  **a. By whom will the required data be extracted from the patient records?**  **b. Are the individuals who extract the required data from the patient records authorized to do so on the basis of a treatment relationship with the respective patients?**  **c. If the answer to question 4.8 is no: are the individuals who extract the data from the patient records under the direct supervision of a clinician who, by virtue of a treatment agreement, is authorized to access the records? If so, please state the name and position of the relevant clinician(s).** | The data is extracted from the file by an external party, as described in the governance document of the ELAN data warehouse: <https://www.lumc.nl/sub/4070/att/1914340/ELAN-Gov-okt2019>.  The external party is the Foundation for Information Provision for Care and Research (STIZON), which has entered into a service and processing agreement for this with the general practitioner. STIZON is ISO 27001 and NEN 7510 certified.  No.  Yes, the general practitioners (patients' caregivers) have instructed STIZON (see above) to extract and provide pseudonymized patient data from the general practitioner information system for the ELAN data warehouse. Processor agreements and / or service agreements have been signed for this between GPs and the data supplier. |
| **4.9**  **Will personally identifiable data be made available to the researcher(s)?** | No, conversion to individual natural persons is reasonably prevented. Analyzes are performed in the secure setting of CBS. Before the results can be exported from the CBS environment, the CBS carries out a mandatory output check where the risk of disclosure is checked. Every result from this research must comply with the output guidelines of the CBS (see Appendix B). For example, all tables and similar output must contain at least 10 units (unweighted) as the basis for each cell or data point. In this way it is independently tested and guaranteed that no data traceable to an individual or institution can be used. |
| **4.10**  **If coding takes place: when will coding occur, by whom, and in what manner?** | Coding is done by STIZON and CBS |
| **4.11**  **Has a notification of the intended data processing been submitted via:**  <https://www.albinusnet.nl/weten-en-regelen/juridische-zaken/privacy/meldenverzamelenonderzoeksdata/>**?** | Yes |
| **4.12**  **If applicable: where will the coded data be stored, and who will have access to the coded data?**  **If applicable: where will the uncoded data be stored, and who will have access to the uncoded data?** | The coded data is stored, and a specific research folder assigned to the department disk (I: \) of PHEG. Only the researchers involved ([name] and [name]) and the PHEG data manager have access to this folder.  There is no storage of uncoded data. |
| **4.13**  **What technical and organizational measures have been taken to prevent loss, theft, or unauthorized use of the research data? For example, is a data safe being used?** | The data never physically leaves the research folder of the LUMC or the remote access CBS environment and see 4.12. |
| **4.14**  **By whom is the code key managed?** | STIZON. |
| **4.15**  **Will (research) data be shared with another institution(s) within the Netherlands and/or the EU?** | No. |
| **4.16**  **a. Will (research) data be shared with another institution/organization outside the EU?**  **b. Will the relevant patients be asked for consent to share their personal data with a country outside the EU?** | No.  Not applicable. |
| **4.17**  **How long will the (research) data be retained? If the data will be kept for longer or shorter than the standard retention period of 15 years, please explain why.** | After processing, the research data is returned to ELAN in accordance with the data transfer agreement. The LUMC department PHEG will keep the research data for 15 years. |

1. **Research population**

| **5.1**  **Inclusion criteria** | Adults patients 18 year and older with an acute UTI and registered at an GP office for a least 1 year |
| --- | --- |
| **5.2**  **Exclusion criteria** | Patients younger than 18 years of age.  Patients with antibiotic prophylaxes  UTIs are excluded as an event if   - During pregnancy - within 3 months after giving birth - within 1 year prior to an UTI (wash-our period) |

1. **Statistical analysis**

| **6.1**  **a. Primary outcome**  **b. Secondary outcome** | ***Primary outcome***  What is the association of antibiotic use for any infection with risk for urinary tract infection in adults?   - Odds ratio for an UTI after antibiotic use in the preceding 3 months   - Per infection group, antibiotic for     - All infections     - An UTI     - An infection expect UTI’s   - Per antibiotic (group)   - Per patient group     - Men     - Women < 50 years of age     - Women ≥ 50 years of age   - Social determinants     - SES     - Migrant background   - Combinations of each subgroup   ***Secondary outcome***   - Hazard ratio for an UTI after antibiotic use in the preceding 3 months   - Per infection group, antibiotic for     - All infections     - UTI     - non-UTI   - Per antibiotic group   - Per patient group     - Men     - Women < 50 years of age     - Women ≥ 50 years of age   - Social determinants     - SES     - Migrant background   - Combination of each subgroup - Incidence of an UTI per month |
| --- | --- |
| **6.2**  **a. Statistical analysis primary outcome**    **b. Statistical analysis secondary outcome** | ***Primary outcome***  The Odds ratio for an UTI after antibiotic treatment the preceding 3 months will be calculated through a logistic regression model.  Risk factors and season variability are defined as confounders in this logistic regression model. Risk factors are a history of an UTI, urine incontinence, urolithiasis, pregnancy, urine catheter, anatomical / functional abnormality urinary tract and Type 2 Diabetes Mellitus. An Odds ratio for an UTI will be attributed to each confounder based on a critical literature appraisal.  ***Secondary outcome***  Cox proportional hazard regression models will be used to examine the associations between an UTI after antibiotic treatment the preceding 3 months.  Survival time (in days) was defined as the period between 14 days after the start of the antibiotic treatment and an UTI. The hazard ratio will be adjusted with the previous described confounders (see primary outcome).  The incidence of each UTI will be calculated for each month during 10 years to examine the season variability. |

1. **Appendices and references**

| **7.1**  **Appendix** | **Appendix A (concerning GP-data):**  Patient Brochure (see this link: <https://www.lumc.nl/siteassets/over-het-lumc/partners/elan/elan-folder-nl.pdf>) &  Poster of the ELAN Datawarehouse (see this link: <https://www.lumc.nl/over-het-lumc/partners/elan/>) (including the English version). |
| --- | --- |

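### The primary endpoint is called a 3-month risk but is fixed as a logistic odds ratio, which fits neither the stated self-controlled design nor a comparison of risks

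*Protocol*

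**What the plan says.** Section 3.1 sets the endpoint and its measure in one sentence: "The primary endpoint is risk of a UTI within 3 months after initiation of antibiotic treatment computed as an odds ratio". The event window follows: "An UTI between 2 weeks and 3 months after antibiotic treatment is defined as an event". Section 6.2 fixes the model: "The Odds ratio for an UTI after antibiotic treatment the preceding 3 months will be calculated through a logistic regression model". The measure carries into the subgroups: "For each subgroup, we will calculate an odds ratio for an UTI after antibiotic treatment".

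Section 3.1 also names a self-controlled case series in which patients act as their own controls. In the same paragraph it describes the comparison as one against UTI patients without an antibiotic course.

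On how common the outcome is, section 2.1 gives two figures. After a UTI: "Around 20-30% of women with an initial UTI will experience a recurrent UTI within 3-4 months of initial infection". In primary care per year: "20 cases per 1.000 registered men and 117 cases per 1.000 registered women".

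Other measures are planned. Section 6.1 lists as a secondary outcome "Hazard ratio for an UTI after antibiotic use in the preceding 3 months", and also monthly UTI incidence. Section 3.1 adds: "Descriptive analysis will be performed for exposures, outcomes and covariables for the whole population of analysis and stratified by antibiotic use or not". No risk ratio, risk difference or adjusted absolute risk is named.

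**The concern.** A risk, an odds ratio and a relative incidence are three different quantities, and the endpoint sentence runs the first two together under a design that delivers the third. The aim and the research question are worded as risk, so the headline figure is likely to be read as a relative risk. That reading is nearly harmless where UTI is rare and clearly wrong where it is common. The plan covers both situations, because it analyses antibiotic courses given for a UTI and courses given for other infections, in men and in women.

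Two things are at stake. One is the meaning of the primary result, which at present cannot be stated in a sentence that is true under the named design. The other is the reading of the subgroup results: odds ratios from strata with very different base risks may look like different effects when the relative risks are equal.

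**Working it through.** The protocol gives no expected odds ratio, relative risk or sample size, so it has no figure of its own to reproduce. The two readings of the design are checked in turn.

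**Reading 1: self-controlled case series.** Take a patient with baseline UTI rate λ, a risk window of length e1 after an antibiotic, control time e0, and relative incidence ρ. Given that a UTI occurred, the probability that it fell in the risk window is

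λρe1 / (λρe1 + λe0) = ρe1 / (ρe1 + e0).

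The rate λ cancels. That is the strength of the design, and it is also why the design identifies ρ but not a 3-month risk such as 1 − exp(−λρe1), which needs λ. Neither word in the endpoint sentence, risk or odds ratio, names what is estimated.

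**Reading 2: cohort-type comparison of patients with and without antibiotics.** With p0 the unexposed risk and p1 = RR × p0 the exposed risk,

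OR / RR = (1 − p0) / (1 − p1).

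Inputs:
- After a UTI, women: p0 = 0.20 to 0.30 (section 2.1; treating it as the unexposed risk is an assumption).
- All registered women: 0.117 / 4 = 0.029 per 3 months (section 2.1, quarter of a year, cases taken as first events).
- All registered men: 0.020 / 4 = 0.005 per 3 months (same source and assumption).
- Risk ratios of 1.2, 1.5 and 2: assumptions, since the documents give none.

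Example: p0 = 0.20 and RR = 1.5 give p1 = 0.30. Then OR = (0.30/0.70) / (0.20/0.80) = 1.714, and 1.714 / 1.5 = 1.143, an excess of 14%.

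| Unexposed 3-month risk | OR at RR 1.2 | OR at RR 1.5 | OR at RR 2 |
|---|---|---|---|
| 0.5% (men) | 1.201 (+0.1%) | 1.504 (+0.3%) | 2.010 (+0.5%) |
| 2.9% (women) | 1.207 (+0.6%) | 1.523 (+1.5%) | 2.062 (+3.1%) |
| 20% (after a UTI) | 1.263 (+5.3%) | 1.714 (+14.3%) | 2.667 (+33.3%) |
| 30% (after a UTI) | 1.312 (+9.4%) | 1.909 (+27.3%) | 3.500 (+75.0%) |

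If 20-30% is taken as the exposed risk instead, the excess is smaller: 8-14% at RR 1.5 and 13-21% at RR 2.

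Reading down a column shows the subgroup point. One risk ratio of 1.5 appears as an odds ratio of 1.50 in men, 1.52 in all women, and 1.71 to 1.91 after a UTI.

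**Which risks the data could give.** Section 3.5 lists antibiotic prescriptions for patients with a UTI and only yearly counts for everyone else. Section 5.1 includes adults with an acute UTI. Section 4.5 says that data of all adults in the warehouse are used. On the list in 3.5, follow-up after an index UTI has a denominator. Courses for other infections in people who never have a UTI do not.

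**The case against.** The strongest objection is that the odds ratio is a valid measure of association and that the formula above assumes a cohort, which is not the design named in 3.1. Both halves are right. The second moves the problem rather than removing it: under the named design the label is wrong for a different reason. A logistic model conditioned on the patient could be set up to estimate the relative incidence, but the result would still be neither a 3-month risk nor best called an odds ratio.

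The subgroup argument is partly a choice of scale. A constant odds ratio gives varying risk ratios just as a constant risk ratio gives varying odds ratios. What stands is a caution on interpretation, because the protocol asks to what extent an increased risk holds across groups.

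The odds ratio is the only primary measure, but it is not the only one in the study. The hazard ratio, monthly incidence and descriptive outcomes by exposure soften the point, though none gives an adjusted 3-month risk contrast.

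The wash-out in 5.2 may remove early recurrences and so make the outcome rarer than 20-30% in the analysed data. That cannot be settled from the text as it stands, and it should not be used to argue in either direction.

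A reader might also infer one headline overstatement by setting the 20-30% after a UTI against the 2.9% in all registered women, which gives 21-39%. The documents do not support this. It compares women with a recent UTI to the general female population, implies a risk ratio of about 7 to 10 that the protocol nowhere claims, and is not an antibiotic effect.

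**Conclusion.** The point holds in a limited form. The primary measure is mislabelled under either reading of the design: a self-controlled analysis yields a relative incidence, and a cohort-type comparison of UTI patients yields an odds ratio for an outcome that section 2.1 suggests is common.

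The size under the cohort reading depends on the base risk and on a risk ratio that the documents do not state. With 20-30% as the unexposed risk it is about 5-9%, 14-27% and 33-75% at assumed risk ratios of 1.2, 1.5 and 2. At the general incidences it is at most about 3% for risk ratios up to 2. The 20-30% figure is for women, covers 3-4 months from infection and is not split by exposure, while the planned window starts at 2 weeks and ends at 3 months and both sexes are studied. It is therefore an illustration and not a prediction. The finding does not mean that the logistic odds ratio is invalid as an association, or that every planned estimate is materially inflated.

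**What to change.** In 3.1, 6.1 and 6.2, choose the measure to match the design and use one name for it throughout.

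- For the self-controlled analysis, make the relative incidence (incidence rate ratio) for the stated risk window the primary measure, and drop the labels odds ratio and risk.
- Where a cohort-type logistic model is kept and the data include people who stay free of a further UTI, for example follow-up after an index UTI, report standardised 3-month risks, the risk ratio and the risk difference beside the odds ratio. Do not promise these for courses without such a denominator.
- State that odds ratios will not be read as relative risks when strata are compared.

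The cost is rewording in three sections and a little more analysis where the cohort-type model is kept. The headline ratio may look less striking.

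### Section 3.1 makes a preceding antibiotic part of the event definition, which contradicts the protocol's own comparator and leaves no rule for counting reference UTIs

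*Protocol*

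**What the plan says.** Section 3.1 first states "An antibiotic treatment is defined as the exposure" and then "An UTI between 2 weeks and 3 months after antibiotic treatment is defined as an event". The second sentence is the only explicit definition of an event in the protocol. The endpoint in the same section is also tied to a preceding course: "The primary endpoint is risk of a UTI within 3 months after initiation of antibiotic treatment computed as an odds ratio".

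Other text treats the outcome more broadly:

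- The comparison in 3.1 is made "compared to patients with an UTI who did not receive an antibiotic treatment".
- The design in 3.1 is a self-controlled case series: "With the SCCS design, patients will be their own control".
- Section 3.1 plans to describe outcomes separately for antibiotic users and non-users.
- Section 5.2 lists when UTIs do not count as events (pregnancy, the period after birth, the wash-out) and does not mention antibiotic exposure.
- Section 6.1 gives the primary outcome as "Odds ratio for an UTI after antibiotic use in the preceding 3 months".

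Under 6.2 the primary odds ratio "will be calculated through a logistic regression model". For the secondary Cox analysis, "Survival time (in days) was defined as the period between 14 days after the start of the antibiotic treatment and an UTI".

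**The concern.** An odds ratio or rate ratio compares how often the same outcome occurs with and without exposure, so the outcome must be defined without reference to the exposure. Section 3.1 makes a recent antibiotic a condition of the event. A UTI with no earlier course is then not an event, and neither is a UTI long after a course. Those are the UTIs that the reference side of the comparison needs.

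At stake is the primary result and every subgroup odds ratio in 6.1 (infection type, antibiotic, patient group, social determinants and their combinations), since all inherit the same definition. If the analysts set the literal rule aside, they must decide for themselves which UTIs and which time count as unexposed. That decision would be taken on data that already exist, and the two sides could end up counted by different rules.

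**Working it through.** The protocol states no event count, power or sample size, so there is no figure of its own to reproduce. The check is structural, followed by a numerical illustration.

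**Step 1. Apply the literal rule to three example records.**

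- Course on 1 March, UTI on 1 May (61 days later): inside the window, so an event, exposed.
- UTI with no earlier antibiotic: not an event.
- Course on 1 January, UTI on 1 June (151 days later in a non-leap year): not an event.

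Only UTIs in the post-antibiotic window qualify. This holds for any choice of window limits.

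**Step 2. Put this into the odds ratio.** Let a and b be exposed events and non-events, and c and d unexposed events and non-events. Then OR = ad/(bc). The rule forces c = 0, so the ratio has no finite value. A self-controlled analysis under the same rule has no events in baseline time and fails in the same way.

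**Step 3. Illustrate with numbers.** Inputs:

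- UTI incidence in women of 117 per 1,000 per year (section 2.1). This is a general-practice figure, used only for scale.
- A window from day 14 to day 91, so 91 − 14 = 77 days (3 months taken as 91 days).
- Assumed, not in the protocol: 10,000 exposed and 10,000 unexposed windows, and true odds ratios of 1.0, 1.5 and 2.0.

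Window risk without an antibiotic effect: 1 − exp(−0.117 × 77/365) = 0.0244, or about 244 UTIs per 10,000 windows.

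| True OR | Exposed UTIs | Unexposed UTIs, any UTI counted | OR, any UTI counted | Unexposed events, literal rule | OR, literal rule with 0.5 added to each cell |
|---|---|---|---|---|---|
| 1.0 | 244 | 244 | 1.00 | 0 | about 501 |
| 1.5 | 361 | 244 | 1.50 | 0 | about 750 |
| 2.0 | 476 | 244 | 2.00 | 0 | about 1,001 |

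For the first row under the literal rule: (244.5 × 10,000.5)/(9,756.5 × 0.5) ≈ 501. A logistic fit to the same data does not converge. The slope is 2.9, 7.9, 17.9 and 27.9 after 5, 10, 20 and 30 iterations, while its standard error rises from 0.17 to about 43,000. The large values are artefacts of the definition. Once the event is separated from the exposure, the true odds ratios are recovered.

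**Step 4. See whether the rest of the text supplies the missing rule.** The comparator names UTI patients without antibiotic treatment, but section 5.1 admits only patients with an acute UTI. At patient level, the literal rule gives that comparator group no events. If any UTI is the event, every patient in the group has one, and there are no non-events. Neither patient-level table works. The comparison has to be made on exposed and reference time, and the protocol does not say what reference time is.

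**Step 5. Check the Cox analysis.** Survival time in 6.2 starts at a point fixed by an antibiotic course. Unexposed patients or time have no origin, so no reference hazard is defined either.

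**The case against.** The strongest reply is that the event sentence should be read in context. It directly follows the definition of exposure, and the next sentences explain why the first 2 weeks are left out, which is how one justifies a risk window. The named comparator, the self-controlled design, the exposure-neutral exclusions in 5.2, the descriptives by antibiotic use and the wording of 6.1 all presuppose UTIs without recent antibiotics. On that reading the authors meant any eligible UTI as the outcome, and the sentence in 3.1 is loosely worded. A model run on the literal rule would also fail visibly at first fit, so it is unlikely to produce a wrong result unnoticed.

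This reply stands as far as intent goes. A reader might infer from 3.1 that the study is bound to produce an infinite odds ratio. The protocol does not support that, because its other sections point the analyst elsewhere. A reader might also want to state what share of UTIs would be lost. The protocol gives no prescription rate. A calculation that treats courses as independent of UTIs would be implausible here, since the cohort consists of UTI patients and section 2.1 says most can be treated with oral antibiotics. No such share is claimed.

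The reply does not remove the contradiction. None of the other text withdraws the definition in 3.1, says which events and time are unexposed, or gives the Cox model a reference origin. Nor is this a detail left to a later analysis plan: the protocol fixes the event, in a form that conflicts with its own comparison. The separate question of combining a self-controlled design with a between-patient comparator and logistic regression is not counted here.

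**Conclusion.** The point holds as a self-contradiction in the primary event definition. Read literally, section 3.1 leaves zero reference events in the primary analysis and all its subgroups. That result depends on no assumed rate, effect or window. The 10,000 windows and the true odds ratios above are illustration only. Read with the rest of the protocol, the likely intent is any eligible UTI, so the practical consequence is an undefined reference side and a rule made up during analysis. Because this concerns the primary outcome, and the Cox analysis shares the gap, it should be corrected before the analysis is run.

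**What to change.** In 3.1, 6.1 and 6.2, separate outcome from exposure and use the same wording throughout:

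- **Event:** any eligible UTI (ICPC U70 or U71, meeting 5.2), regardless of earlier antibiotic use.
- **Exposed time:** from 2 weeks to 3 months after the start of a course. Bring the endpoint sentence in 3.1, which has no lower limit, into line with this.
- **First 2 weeks after the start of a course:** a separate state, neither exposed nor reference.
- **Reference time:** the patient's other observed time, with UTIs counted by the same rule as in exposed time.
- **Primary model:** fitted to this exposed and reference time structure, not to a patient-level table.
- **Cox model:** state the time origin for reference time that matches the origin for exposed time.

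The cost is rewording the three sections and some restructuring of the analysis dataset into exposure states. No new data are needed, because section 3.5 already covers all patients with a UTI and their J01 prescriptions.
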